## Abstract

**Background:**

Type 2 diabetes mellitus (T2DM) is a critical global health issue, especially in low- and middle-income countries like Afghanistan and Pakistan, where many cases remain undiagnosed and specialized care is costly. Community Health Participatory Research, which actively involves community members in addressing health issues, is increasingly recognized as an effective approach to deliver sustainable and culturally relevant health solutions. Participatory Learning and Action (PLA), a method of Community Health Participatory Research, was implemented in the D-Magic (Diabetes Mellitus: Action Through Community Groups or mHealth Information for Better Control) trial in Bangladesh that empowered communities to identify challenges and develop locally relevant strategies to prevent and control T2DM.

**Objective:**

This study aims to adapt the PLA-based D-Magic intervention for the prevention and control of T2DM in rural and urban communities of Afghanistan and Pakistan.

**Methods:**

This trial, titled “Engagement of Community Through Participatory Learning and Action for Control and Prevention of Type 2 Diabetes and Its Risk Factors” (EMPOWER-D), will systematically adapt the D-Magic intervention using the ADAPT guidance framework. The study will be conducted across 3 sites: rural Afghanistan (Kabul), rural Pakistan (Peshawar and Swabi), and urban Pakistan (Karachi). Stakeholders and community members will be involved to ensure cultural relevance and authenticity. The process includes identifying barriers and facilitators to the implementation of community-based interventions through a qualitative study and a scoping review, co-designing intervention materials, and piloting for feasibility and effectiveness.

**Results:**

EMPOWER-D was funded and launched in November 2022 by the United Kingdom’s National Institute for Health and Care Research (NIHR203248). Following a year-long development phase, the adaptation protocol was finalized, and a mock run of the interviews was conducted. Recruitment and qualitative data collection, including in-depth interviews and focus group discussions, began in July 2024 and have been completed in Peshawar, Swabi, and Karachi. As of January 2025, data collection has commenced in Afghanistan. Results are anticipated to be published in mid-2026 following the completion of data analysis.

**Conclusions:**

The EMPOWER-D adaptation will align the PLA-based intervention with the local sociocultural context, ensuring health equity and participation. Building on the D-Magic trial’s success, this adaptation will ensure the intervention’s effectiveness and cost-effectiveness in preventing and managing T2DM, not only in Afghanistan and Pakistan but also in other low- and middle-income countries.

## Introduction

### Background

Type 2 diabetes mellitus (T2DM) is a major global health issue, with 463 million adults affected globally, 80% of whom are living in low- and middle-income countries (LMICs) [1]. This health crisis is further exacerbated by conflicts, political instability, and natural disasters that disproportionately affect LMICs [2,3] such as Afghanistan and Pakistan. Afghanistan faces significant challenges, with an estimated 11.07% of adults having T2DM and 10.32% having impaired hyperglycemia [4]. Similarly, in Pakistan, the world’s fifth most populous country, 26.7% of adults (approximately 33 million people) have T2DM [5]. Additionally, many cases of T2DM in both countries are undiagnosed, worsening the health and economic burden of the condition.

Environmental changes, epidemiological transition, genetic predisposition, and behavioral factors such as diet and physical inactivity contribute to the rising incidence of T2DM in LMICs, in countries such as Afghanistan and Pakistan [6,7]. The disease impacts physical health, imposing significant emotional, social, and economic strains on individuals and communities [8]. T2DM resulted in 75.3 million (95% uncertainty interval 63.5‐90.2) global disability-adjusted life years in 2021 and was responsible for 2.6% (95% uncertainty interval 2.3%‐2.9%) of total global disability-adjusted life years [9].

Recent advances in health care have suggested addressing T2DM through specialized care, including a multidisciplinary approach to address diabetes-related complications [10]. However, this approach places a continuous and significant burden on individuals due to high out-of-pocket costs [11,12] for frequent medical visits, expensive medications, and diagnostic tests. Furthermore, the focus is usually placed on the management rather than the prevention of the disease, which further adds strain on already stretched health care systems, making diabetes management less accessible for many. In contrast, community-based participatory approaches are becoming increasingly popular because of their effectiveness in improving diabetes outcomes [13]. Moreover, community-based participatory approaches to health address the underlying causes of the disease and help in the prevention as well as the management of the health issue [14].

Community Health Participatory Research (CHPR) is an inclusive approach that actively involves community members in identifying areas for intervention, defining the problem, and generating potential solutions [15]. These approaches prioritize collaboration, equity, and the cocreation of knowledge to produce more relevant and effective interventions [16]. One CHPR approach is Participatory Learning and Action (PLA). PLA was inspired by Paulo Freire’s philosophy, where community members actively participate in learning about, defining, and addressing their health issues through facilitated sessions and activities [17]. PLA empowers marginalized communities to identify and solve their problems through a cycle of problem identification, solution planning, implementation, and reflection rather than relying on top-down strategies [18]. PLA has been systematized into a group-based intervention and has proven effective in improving neonatal and child health [19,20]. More recently, this approach was adapted to address diabetes in rural Bangladesh through the D-Magic (Diabetes Mellitus: Action Through Community Groups or mHealth Information for Better Control) trial [21]. The PLA intervention that was tested led to a 48% reduction in the prevalence of T2DM compared to the control group (305/3757, 8% vs 493/3821, 13%, respectively), with an adjusted odds ratio of 0.52 (95% CI 0.38‐0.71; *P*<.001). Additionally, the intervention increased awareness of T2DM prevention and motivated healthy dietary changes [21]. The D-Magic trial successfully used a participatory approach, organizing communities into small groups that held monthly meetings led by a lay facilitator. These groups followed a 4-phase PLA cycle to prevent and control T2DM, identifying barriers to healthy behavior and developing and implementing context-specific strategies, such as raising awareness, group exercise, income generation, and kitchen gardening [21].

The EMPOWER-D (Engagement of Community Through Participatory Learning and Action for Control and Prevention of Type 2 Diabetes and Its Risk Factors) trial is grounded in the conviction that PLA can empower communities to take ownership of diabetes prevention and control efforts. By organizing communities for collective action, PLA aims to increase awareness and motivation for healthy behaviors, thereby enabling individuals to make informed choices about their health. As a result, individuals are expected to gain confidence and motivation to seek health care services and adopt healthier habits. Ultimately, this approach is anticipated to lead to the development of a self-sustainable model for the prevention and control of diabetes, which can also have a positive impact on the prevention and control of other noncommunicable diseases (NCDs) in the region.

The theory of change logic model for our PLA intervention in EMPOWER-D (Multimedia Appendix 1) illustrates the hypothesized pathways through which participatory group activities are expected to lead to improved diabetes prevention and control in fragile LMIC contexts. It was developed by the research team, based on the findings from the D-Magic process evaluation and the context of Pakistan and Afghanistan. This model underpins our adaptation approach and will guide both implementation and evaluation.

Participatory interventions like PLA are highly context-sensitive, requiring adaptation to achieve sustainable outcomes when implemented in new settings or with different populations [22]. Despite its effectiveness and greater acceptability among the people, evidence on how PLA interventions like D-Magic can be adapted for fragile, crisis-affected, and socially diverse LMICs remains scarce. This is particularly relevant in countries with high T2DM burdens, such as Afghanistan and Pakistan, where direct replication could overlook important contextual distinctions [23,24]. These include variations in health care system capacity, cultural differences, gender-segregated communities, urban-rural disparities, and the added burden of conflict and political instability [25]. In Afghanistan, decades of conflict have overshadowed public health efforts, including addressing NCDs like T2DM, likely resulting in underreported prevalence [26]. In Pakistan, although the situation is relatively stable, the country has faced repercussions due to its proximity to unstable regions and a rapidly changing political environment, which adds to the issues of rapid urbanization and health care disparities, particularly between urban and rural areas, and for women in conservative rural regions [27]. These challenges contribute to rising T2DM rates and a fragmented health care system, with private urban centers offering better care than underfunded public clinics [28].

These differences shape how communities perceive health, engage with interventions, and mobilize collective actions. Thus, this study does not aim for simple transferability of D-Magic but for systematic adaptation that will generate new evidence on how participatory approaches can be tailored for fragile, gender-segregated, and highly diverse LMIC contexts.

### Aims and Objectives

This work aims to provide the following:

Empirical insights into barriers and facilitators of community-based diabetes prevention in crisis-affected and urbanizing LMICsMethodological advances by combining scoping reviews, qualitative inquiry, and co-designPractical frameworks for incorporating participatory diabetes interventions in health systems where trust, equity, and access are major challenges.

## Methods

### Ethical Considerations

Ethical approval for this study has been granted by the ethics review committees of the Aga Khan University, Karachi, Pakistan (2024-9340-28927); Khyber Medical University, Peshawar, Pakistan (KMU/IPHSS/Ethics/2023/EO/0136); HealthNetTPO, Kabul, Afghanistan (A-12-24-464); and the National Bioethics Committee (NBC-R-1070). Researchers will approach identified participants and inform them about the research verbally and through a participant information sheet in their local language (Pashto, Dari, and Urdu). Participants will be encouraged to ask about the research before deciding whether they would like to participate. For those who consent to participate and provide a written consent, a time and date for an in-depth interview (IDI) or focus group discussion (FGD) will be arranged. Interviews will be conducted in a comfortable and confidential environment to ensure participants’ privacy. Participants will be assigned unique identification codes, and no personal identifiers will be included in transcripts or analysis files. Audio recordings will be stored in password-protected, encrypted folders and deleted after transcription. Deidentified transcripts will be used for analysis. All electronic data will be stored on secure, password-protected devices, and hard copies (eg, consent forms) will be kept in locked cabinets. Only authorized research team members will have access to the data, and findings will be reported in aggregate to protect participant identity. Participants will receive a monetary incentive to cover their travel expenses and compensate them for their time spent participating in the interview.

The full version of the EMPOWER-D trial is registered with ClinicalTrials.gov (NCT07350694 for rural Afghanistan, registered January 20, 2026, NCT06561126 for rural Pakistan, registered August 23, 2024, and NCT06570057 for urban Pakistan, registered August 26, 2024).

### Study Overview

This study is part of the research program EMPOWER-D. The EMPOWER-D trial, a project of Centre for Improving Mental and Physical Health Together (C4IMPACT), was launched to specifically address the prevention and control of T2DM in rural and urban communities of Afghanistan and Pakistan.

### Conceptual Framework

We will utilize the ADAPT guidance [22] to adapt the intervention systematically. The ADAPT guidance framework emphasizes the importance of involving stakeholders and community members in the adaptation process to ensure that the adapted evidence-based intervention (EBI) is culturally appropriate and contextually relevant.

The framework comprises 5 steps to guide the adaptation process (Figure 1). This study will adapt the D-Magic intervention by carrying out three main activities: (1) identifying the barriers and facilitators in the implementation of community-based interventions (CBIs) and their contextual appropriateness through a qualitative study (using the socioecological model (SEM) [29]) with local stakeholders and a scoping review of the published literature, (2) co-designing the intervention materials, and (3) piloting the adapted materials for feasibility and effectiveness.

The adaptation of intervention materials across the 3 sites (rural Afghanistan, rural Pakistan, and urban Pakistan) will vary according to each context, but the process of adaptation will be the same. The process and findings will be documented using the FRAME (Framework for Reporting Adaptations and Modifications in Evidence-based Interventions) framework [30] (Figure 1), detailing the changes made, the reasons for these changes, and the implementation procedures. The outcomes and implications of the study will be recorded and reported, with recommendations for future research and practice.

**Figure 1. F1:**
[figure not shown]
Conceptual framework of the process of adaptation in EMPOWER-D (Engagement of Community Through Participatory Learning and Action for Control and Prevention of Type 2 Diabetes and Its Risk Factors). FRAME: Framework for Reporting Adaptations and Modifications in Evidence-Based Interventions; LMICs: low- and middle-income countries; NCDs: noncommunicable diseases; PLA: Participatory Learning and Action; T2DM: type 2 diabetes mellitus; PICO: Population, Intervention, Comparison, Outcome.

### Phase 1: Identifying Barriers and Facilitators to the Implementation of CBIs

#### Step 1A: Qualitative Study

##### Overview

We will conduct a qualitative study to explore the understanding of T2DM in rural and urban communities of Pakistan and Afghanistan, the barriers and facilitators to the uptake and maintenance of healthy behaviors related to T2DM, and their willingness to engage in CBIs. We selected a qualitative approach because health-related behaviors are deeply shaped by cultural beliefs, gender roles, and community structures that cannot be adequately captured through quantitative methods. Qualitative inquiry will also allow us to capture the lived experiences and perspectives of diverse community stakeholders, contributing to context-rich insights that are essential for tailoring participatory interventions to fragile and heterogeneous settings. The SEM emphasizes the interaction of individual, interpersonal, organizational, and community-level factors in shaping health outcomes [28]. The SEM was preferred as it offers a comprehensive framework to explore diabetes-related barriers and facilitators across multiple levels, which is essential for designing and adapting CBIs.

##### Study Settings

In Afghanistan, the feasibility trial will be conducted in Farza and Dehsabz, Kabul district. The trial will mainly focus on the rural population in the Kabul district, which is populated mainly by people from lower socioeconomic backgrounds. Protracted conflicts and political instability have greatly affected the health care system in the district.

In Khyber Pakhtunkhwa, the trial will be conducted in the districts of Peshawar and Swabi. Peshawar, the densely populated capital, has 4.7 million [31] residents and offers comprehensive health care through public and private sectors. Swabi, with 1.9 million people [31], provides primary and secondary care through government facilities supplemented by private health care. Both predominantly rural districts, inhabited by Pashtuns, faced challenges of poverty, limited infrastructure, under-resourced education, and conflicts, resulting in reduced economic growth and development for the past decade.

For the urban feasibility trial in Pakistan, the District Central of Karachi, Sindh, has been selected. With a population of approximately 3.8 million [32], it is one of the most densely populated areas in Karachi, which itself houses 17 to 20 million people. The district’s diverse population includes various ethnic groups, and livelihoods range from white-collar jobs to informal labor. Education access is uneven, with significant disparities between elite private schools and underfunded public institutions. Karachi’s extensive health care system includes public, private, and nonprofit sectors, but it faces overcrowding and unequal access, particularly in public hospitals.

##### Participants and Recruitment

Participants will be recruited through purposive sampling from the 3 study sites. The inclusion criteria are adult (over 18 y of age) male and female participants residing within the geographical boundaries of the selected sites. Participants must be able to communicate effectively in either Pashto, Urdu, or Dari (or any other local language) for the interviews and be willing to share their experiences and opinions openly. Participants who have already participated in similar interviews or focus groups for the same study will be excluded to avoid redundancy and bias. Maximum variation will be ensured by recruiting participants with different demographic characteristics (gender, socioeconomic status, geographical spread, age, ethnicity, etc). A team of male and female researchers will go to the field to recruit participants through their professional contacts and snowballing. In addition, community advisory panels (CAPs) were formed at all study sites, comprising members of the community, such as religious leaders, community elders, health care professionals, individuals living with T2DM, and caregivers. These CAP members will also be requested to help identify potential participants.

##### Sampling

Five categories of stakeholders, guided by the SEM, will be recruited to explore the views and perspectives of people living with T2DM and people with unknown T2DM status, carers, influential people, and health care providers (Table 1).

Specifically, we will recruit the following:

Carers of people with T2DM, adults who are the primary caregivers for someone living with T2DM, are to provide insights into household dynamics and support systems.People with unknown T2DM status, adults who have never been diagnosed with T2DM, and who do not self-identify as having the condition. This group may include individuals with undiagnosed T2DM, as they are unaware of their glycemic status at the time of recruitment, to capture perceptions, beliefs, and practices around prevention, lifestyle, and risk awareness.Influential people, Imams (religious leaders), community elders, teachers, elected representatives, etc, are engaged, given their influence on collective norms and decision-making.A range of health care providers, including doctors, nurses, pharmacists, and community health workers, who treat and care for people with T2DM will be interviewed to reflect organizational and health system perspectives.People with T2DM, adults living with T2DM (who have had a medical diagnosis), to capture both lived experiences of disease management and perceptions of risk and prevention.

As shown in Table 1, a total of 60 IDIs and 16 FGDs with the aforementioned 5 categories of participants will be conducted at each site. Efforts will be made to recruit an equal number of male and female participants across the study sites. In line with qualitative research principles, our sampling strategy is guided by the principle of thematic saturation. The planned sample size is sufficiently large to capture a diverse range of perspectives across major stakeholder groups while allowing flexibility to adjust numbers until saturation is reached.

**Table 1. T1:** Participants’ categories and sample size for in-depth interviews (IDIs) and focus group discussions (FGDs).

Participants’ category and interview type	Sample size			
	Rural Pakistan (Peshawar and Swabi)	Urban Pakistan (Karachi)	Rural Afghanistan (Kabul)	Total sample
People living with T2DM^a^				
IDIs	4	4	4	12
FGDs	4	2	2	8
People with unknown T2DM status				
IDIs	4	4	4	12
FGDs	4	2	2	8
Carers of people with T2DM				
IDIs	4	4	4	12
Health care providers				
IDIs	4	4	4	12
Community influentials				
IDIs	4	4	4	12

a T2DM: type 2 diabetes mellitus.

Data saturation will be evaluated through an iterative process of concurrent data collection and analysis. After each round of interviews and FGDs, the research team will review the transcripts to identify emerging codes and themes. Saturation will be considered reached when successive interviews no longer yield new codes or meaningfully expand existing categories. To enhance rigor, at least 2 researchers will independently assess saturation and maintain a saturation grid to document the point at which no new information emerges. This approach ensures a clear, evidence-based justification for the adequacy of the sample and the credibility of the findings.

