##### Data Collection

The IDIs and FGDs will be conducted by a team of male and female research assistants trained in qualitative research methods. An experienced research team member will supervise the fieldwork. The research team will develop topic guides based on the research objectives and the conceptual framework. FGDs and IDIs are valuable research techniques, and by triangulating these methods and participants, we aim to obtain rich information from various sources. The data collection techniques are described below:

In-depth interviews: Interviews will be conducted by research assistants with support from a notetaker and are expected to last 45 to 60 minutes. IDIs will be conducted with all 5 categories of participants in a peaceful place convenient to them. With participants’ consent, interviews will be recorded using a digital audio recorder (Multimedia Appendices 2-6).Focus group discussions: FGDs will involve people living with T2DM and people with unknown T2DM status to foster interactive discussions and gain insights into community beliefs and experiences. Separate FGDs will be held for males and females and those with T2DM and with unknown T2DM status to capture diverse perspectives. Discussions will occur at convenient locations, such as local community centers or public spaces, and will be facilitated by a moderator and a notetaker and are expected to last 60 to 90 minutes. With participants’ consent, FGDs will be audio-recorded (MultimediaAppendices 7  8).

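### The Sampling text gives 60 IDIs and 16 FGDs for each site, but in Table 1 these are the totals over all three sites, so the per-site sample is overstated threefold for IDIs and two- to fourfold for FGDs

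*Protocol article*

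**What the plan says.** The Sampling section of the protocol article names five participant categories and then, pointing to Table 1, states that "a total of 60 IDIs and 16 FGDs with the aforementioned 5 categories of participants will be conducted at each site". A little further on it says: "The planned sample size is sufficiently large to capture a diverse range of perspectives across major stakeholder groups". It adds that numbers may be adjusted until saturation is reached.

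Table 1 is captioned as giving the categories and the "sample size for in-depth interviews (IDIs) and focus group discussions (FGDs"). It has one column for each of the three sites and a total column. Each of the five categories has an IDI row, and two of them also have an FGD row.

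The Data Collection section agrees with that layout. On interviews it says "IDIs will be conducted with all 5 categories of participants"; on focus groups, "FGDs will involve people living with T2DM and people with unknown T2DM status".

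The number of sites is clear. Participants and Recruitment says "Participants will be recruited through purposive sampling from the 3 study sites", and the abstract lists them: "The study will be conducted across 3 sites: rural Afghanistan (Kabul), rural Pakistan (Peshawar and Swabi), and urban Pakistan (Karachi"). Peshawar and Swabi together are one site.

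The Data Analysis section says that the three sites are analysed separately, with a report for each and a combined summary afterwards.

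**The concern.** The sentence offers its figures as a reading of Table 1, yet it gives as per-site counts the numbers that the table shows as totals over all sites. The two statements cannot both hold.

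The stake is what a reader believes to lie behind each site report. Because the sites are analysed separately, the per-site count is the working sample of each analysis, and it is the count that is misstated. Someone relying on the text would expect 60 interviews and 16 focus groups behind the Karachi report; Table 1 plans 20 and 4. The same gap would affect anyone who budgets fieldwork from the text, or who later compares achieved with planned numbers.

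The same sentence has a smaller fault: it links the FGDs to all five categories, when only two have them.

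**Working it through.** **Inputs, all from Table 1.** Each of the five categories has 4 IDIs in rural Pakistan, 4 in urban Pakistan and 4 in rural Afghanistan, with a row total of 12. Each of the two FGD categories has 4, 2 and 2 FGDs, with a row total of 8.

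**Step 1: reproduce the stated figures.** Summing over categories and sites:

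- IDIs: 5 × (4 + 4 + 4) = 5 × 12 = 60
- FGDs: 2 × (4 + 2 + 2) = 2 × 8 = 16

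Both figures in the text are reproduced exactly, as totals over the three sites.

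**Step 2: the same sums by site, against the text.**

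| Site | IDIs, Table 1 | IDIs, text | Ratio | FGDs, Table 1 | FGDs, text | Ratio |
|---|---|---|---|---|---|---|
| Rural Pakistan | 5 × 4 = 20 | 60 | 3 | 2 × 4 = 8 | 16 | 2 |
| Urban Pakistan | 5 × 4 = 20 | 60 | 3 | 2 × 2 = 4 | 16 | 4 |
| Rural Afghanistan | 5 × 4 = 20 | 60 | 3 | 2 × 2 = 4 | 16 | 4 |
| All sites | 60 | 3 × 60 = 180 | 3 | 16 | 3 × 16 = 48 | 3 |

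No site column gives 60 or 16.

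**Step 3: could something else explain the mismatch?**

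- *A damaged table.* Every row total equals the sum of its site cells (4 + 4 + 4 = 12; 4 + 2 + 2 = 8), and the grand totals match the 60 and 16 in the text. The table is intact.
- *Another meaning of site.* Counting Peshawar and Swabi as two sites would divide the rural Pakistan column (20 IDIs, 8 FGDs) between them. That makes the per-site counts smaller and moves them further from 60 and 16.
- *Extra recruitment until saturation.* The sentence says what Table 1 shows. It does not describe an enlarged target.

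**Step 4: categories.** Table 1 has FGD rows for people living with T2DM and for people of unknown status only. Carers, health care providers and community influentials have IDIs alone. Data Collection says the same.

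**The case against.** The strongest reply is that little harm is done. The wrong phrase points to Table 1, which follows in the same section, is correct, and gives every per-site cell, so an attentive reader can recover the intended numbers at once. Table 1 is itself a sample size statement. This is a purposive qualitative sample with no power, error rate or estimate at stake, and its size may change until saturation. The reference to five categories can be read as covering IDIs and FGDs jointly.

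Most of this stands, and it limits the weight of the point. It does not remove the contradiction, because no reading of the sentence agrees with the table it cites.

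A reader might infer more than the documents support:

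- *That the claim of a sufficiently large sample rests on the wrong figure.* That claim names no number. It refers to the planned sample, which Table 1 sets out correctly. The article then grounds adequacy in a procedure: concurrent analysis, at least two independent assessors and a saturation grid.
- *That saturation cannot be reached within a category or sex, or that rural Pakistan has only about one interview per district-by-sex cell.* The article defines no such strata for the IDIs and claims no saturation at that level. It promises only efforts towards equal numbers of men and women. It gives no minimum number of interviews against which such a shortfall could be measured.
- *That triangulation of IDIs with FGDs must be restricted to two categories.* The article plans triangulation over methods and over participants, and already says who takes part in FGDs.

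**Conclusion.** The sentence is wrong as written. The planned sample in Table 1 is 60 IDIs and 16 FGDs for the whole study: 20 IDIs per site, and 8, 4 and 4 FGDs in rural Pakistan, Karachi and Kabul. Taken literally, the text adds 180 − 60 = 120 IDIs and 48 − 16 = 32 FGDs that the table does not contain.

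This takes Table 1 as the intended plan. The table's internal consistency, and the exact match of its grand totals to the two figures in the text, make a slip in the words about site by far the likeliest cause. It is an error in reporting the sample, and the documents do not show a flaw in the design. Severity is moderate: the error is large in relative terms and affects the number on which each site report rests, but the correct figures stand beside it. The wording about five categories is a minor addition.

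**What to change.** Replace the sentence with, for example: *A total of 60 IDIs (20 per site, covering all 5 categories) and 16 FGDs (8 in rural Pakistan, 4 in Karachi and 4 in Kabul, held only with people living with T2DM and people of unknown T2DM status) will be conducted across the three sites.*

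The adequacy sentence that follows should then be read against these per-site numbers. It needs no new claim about saturation.

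The cost is wording only. Table 1, recruitment and the analysis stay as they are; the stated sample per site becomes smaller and agrees with the table. If the sponsor did intend 60 and 16 at each site, Table 1 would have to be rewritten instead, with 180 IDIs and 48 FGDs in total. The sponsor should confirm that this was not the intention.
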